## Abstract

**Introduction:**

Gesture performance deficits are prevalent in schizophrenia patients and are strongly associated with poor social communication skills and community functioning, affecting their overall quality of life. Currently, video-recording technology is widely used in clinical settings to assess gesture production deficits in schizophrenia patients. Nevertheless, the subjective evaluation of video-recordings can encumber task assessment. The present study will aim to use virtual reality to examine its potential use as an alternative tool to objectively measure gesture performance accuracy in schizophrenia patients and healthy controls.

**Methods:**

Gesture performance in the virtual reality setting will be based on the well-established Test of Upper Limb Apraxia. Participants will be immersed in a virtual environment where they will experience themselves being embodied in a collocated virtual body seen from a first-person perspective. Motion trackers will be placed on participants' hands and elbows to track upper body movements in real-time, and to record gesture movement for later analysis. Participants will see a virtual agent sitting across from them, with a virtual table in between. The agent will perform various types of gestures and the participants' task will be to imitate those gestures as accurately as possible. Measurements from the tracking devices will be stored and analyzed to address gesture performance accuracy across groups.

**Discussion:**

This study aims to provide objective measurements of gesture performance accuracy in schizophrenia patients. If successful, the results will provide new knowledge to the gesture literature and offer the potential for novel therapeutic interventions using virtual reality technologies. Such interventions can improve gesturing and thus advance social communication skills in schizophrenia patients.

## 1. Introduction

Schizophrenia is a complex mental health disorder that affects ~1% of the general population. Schizophrenia is characterized by a wide range of clinical symptoms including disorganized thinking, paranoia, hallucinations, motor abnormalities, executive dysfunction, social withdrawal and affective flattening, all of which greatly disturb social communication processes leading to poor community functioning and quality of life (1–3). Successful social communication is highly dependent on one's ability to correctly perceive, interpret and execute socially relevant cues (4). In recent years, gestures serve as an important research tool in understanding social communication deficits in schizophrenia patients (5, 6).

Gestures are biological movements used alone or in combination with speech, to aid in social communication (7). Video-recordings of gesture performance in clinical settings show that schizophrenia patients and individuals at high-risk for psychosis tend to use hand gestures less frequently, or in the wrong context (8–10) and spend significantly less time fixating on the performed gestures (11). In addition, schizophrenia patients have deficits in correctly imitating meaningless and meaningful gestures following visual demonstration from an experimenter. Errors include slow movements with reduced amplitudes, extra movements, omissions, and body-part-as-object (12, 13). These errors are associated with impairments in postural knowledge, tool use, and social perception, suggesting a generalized impairment in non-verbal social communication in schizophrenia (14). Furthermore, deficits in gesture performance predict poor community functioning (15), and are strongly associated with symptom severity, motor abnormalities, and executive dysfunction, such as processing speed, attention, and working memory abilities (5, 11, 13, 14, 16–23).

Video recordings are easy to implement and have provided rich and notable insights on the mechanisms involved during gesture performance in schizophrenia (13, 14, 20, 24, 25). However, there are a few limitations to consider. In clinical settings, video-recordings can modify naturally occurring behaviors (26). In addition, when video-recordings are used to score participants' performance during a task, the data are categorical in nature and the process requires vigorous training for the scorer(s), which can be time consuming and cause inter-rater reliability issues. Further, the positioning of the camera can differ between sessions and participants' affecting viewpoint and body representations that can alter the evaluation of the task. The use of virtual reality (VR) technology can readily tackle most of these limitations (27).

In recent years, VR is increasingly used in the assessment and rehabilitation of movement execution (28). VR allows the creation of a virtual environment where users can interact with virtual characters via spoken language and hand gestures just as they would in the real world (29), supporting a highly immersive experience with increased ecological validity, reliability and reproducibility (30). Images of the virtual environment are displayed via the use of a head mounted display (HMD) where the users' head position and orientation are continuously tracked and updated as they move around (31, 32). Motion tracking devices can be used to substitute the users' body with a gender-matched virtual one seen from a first-person perspective and onto which their real movements are mapped in real-time, resulting in an illusionary ownership over the virtual body (33–35). Data from these tracking devices are multidimensional and provide an objective, reliable and unobtrusive measurement of real-time human behavior that surpasses that provided by video-recording data (36).

To our knowledge, no study to date has utilized VR to examine accuracy of hand gestures in schizophrenia patients. To this end, the aim of the present study is to apply VR technology to collect measurements of naturally occurring hand gestures during an imitation task in schizophrenia patients and compare their performance to healthy controls. Additionally, we will administer motor, socio-cognitive and community functioning assessments used in previous research from our lab to determine their relationship with hand gesture accuracy in VR. In accordance with previous studies (5, 13, 14, 20), we hypothesize that schizophrenia patients will perform the required gestures less accurately than healthy controls and that these deficits will be linked to their psychopathology, motor abnormalities, as well as compromised socio-cognitive and community functioning.

## 2. Materials and methods

### 2.1. Study design

This is an exploratory cross-sectional observational study using VR technology to assess the performance accuracy of different hand gestures. An HMD will be used to immerse participants in the virtual environment. Motion trackers, attached to the hands and elbows, will provide participants with real-time upper body tracking (see section VR apparatus for more details). Data from the HMD and motion trackers will be continuously stored on a computer for analyses. We plan to recruit 60 schizophrenia patients and 60 age and gender matched controls over a 2-year period. The duration of the study is ~6 h. The assessments are separated into 2-h sessions/per day and all assessments are completed within a 72-h period.

### 2.2. Participants

Schizophrenia patients will be recruited from the inpatient and outpatient departments of the University hospital of Psychiatry and Psychotherapy in Bern, Switzerland. All potential schizophrenia patients will be screened using the Mini International Neuropsychiatric Interview (37) for the DSM-5 criteria. Healthy controls will be recruited through advertisement and by word-of-mouth. Inclusion criteria for all participants include: right-handedness, 18–65 years of age, no substance abuse (except nicotine), and no history of neurological disorders or any other severe mental health disorders. Additionally, for controls only, no personal, or first-degree relatives with a history of any mental health disorders.

### 2.3. Primary outcome

#### 2.3.1. Gesture assessment in VR

The VR gesture task is based on the Test of Upper Limb Apraxia (TULIA), which was developed in accordance with the central domains and semantic characteristics of gesture performance (38, 39). TULIA measures accuracy of finger and hand movements in 48 items across two domains: the imitation domain (gesture performance following visual demonstration from the experimenter) and the pantomime domain (gesture performance following verbal command from the experimenter). Within these domains three different semantic categories of gestures exist: (a) meaningless (new gestures without semantic elements), (b) intransitive (highly learned communicative gestures, such as waving good-bye), and (c) transitive (tool-based gestures, such as using a toothbrush). Scores for each item are rated using a 0–5 scale. The maximum score earned in the TULIA test is 240 (120 per domain), which is indicative of superior gesture performance (38). Administration of the TULIA test requires both the participant and the experimenter to be seated across from each other with a table between them; both with their hands placed flat on the table. For the imitation domain, which is the focus of this study, participants are asked to execute the required gestures with their dominant hand only after the experimenter has demonstrated the gestures in a mirrored manner and has returned their hand to the original position (flat on the table). Participants are informed on the nature of the gestures following each block. The TULIA test is video-recorded and later quantified by an independent experimenter.

### 2.4. VR procedures

The development of the virtual environment for gesture assessment in VR was inspired from clinical applications of the TULIA task and created using the real-time 3D engine Unity 2020 LTS.^1^ Animations for the TULIA movements were recorded using the Glycon 3D^2^ motion capture software and edited with Autodesk MotionBuilder 2019.^3^ The virtual environment consists of an office room equipped with a table in its center (Figure 1A). Windows and a door are also present on the left and right side of the room, respectively. Across from participants, on the other side of the table, a virtual agent is seated on a chair with her hands flat on the table (Figure 1B). Outside the virtual environment, in the physical laboratory, participants are placed in a similar scenario with their hands flat on a table in front of them. Motion trackers are placed on the hands and elbows of each arm, and the HMD is adjusted for each participant (Figure 1C). The HMD provides a stereoscopic display of the virtual environment and of the autonomous agent seen from an embodied first-person perspective, while the motion trackers provide participants with virtual arms that they can control using their own movements. Participants' virtual body will be gender matched. Once immersed in the virtual environment participants will be instructed via pre-recorded verbal instructions to look around and describe what they see. In addition, they will be instructed to move their hands up and down to induce the illusion of body ownership over the virtual body, following earlier examples (33–35). After this introductory phase, participants will be trained on the task. They will be informed to closely look at the movements of the agent seated across from them performing the gestures in a mirrored manner. Their task will be to imitate those same gestures as accurately as possible using their dominant hand (right hand). To ensure that participants perform the gestures only after the agent places her hands back on the table, a red light is added as a visual cue, and participants will be informed to only perform the gestures once this light turns off. Similar to the TULIA task, participants will be informed on the nature of the gestures before each block. Each block contains 6 different gestures and will be repeated twice during the experiment. All gesture blocks (meaningless, intransitive, and transitive) will be randomized across participants. A post-experiment questionnaire will be used to record participants' subjective feeling of presence and embodiment with respect to their virtual body, as well as, other questions related to how participants evaluate the virtual female agent and their interaction, and overall experience using a −3 (“not at all”) to a 3 (“very much”) scale (Table 1). In addition, possible side effects (i.e., dizziness), as well as, personal thoughts and feelings regarding participants' exposure to VR will also be accounted for directly after the experiment and at the follow-up session, 2-weeks after exposure. The VR procedures are demonstrated in Supplementary Movie S1.

**Figure 1 F1:**
[figure not shown]
The virtual reality setup. **(A)** A third-person perspective of the virtual setup depicting the position of the participant on one side of the table and the virtual agent on the other. **(B)** The virtual environment as seen from the participant's first-person perspective. The participant has a view of their own hands and gender-matched body and they can see the virtual agent sitting across from them with the hands resting on the table. **(C)** The participant in the physical laboratory equipped with the HMD and upper body tracking devices.

**Table 1 T1:** The post-VR questionnaire.

**Variable**	**Question**
Body	“How much did you feel that the *virtual body* you saw when looking down at yourself was your own body?” *(−3…3)*
Mirror	“How much did you feel that the *virtual body* you saw when looking at yourself in the *mirror* was your own body?” *(−3…3)*
Agency	“How much did you feel that the movements of the virtual body were caused by your own movements?” *(−3…3)*
Real person	“How much did you feel like the person sitting in front of you was a real person?” *(−3…3)*
Friendly person	“Was the virtual person sitting in front of you friendly toward you?” *(−3…3)*
Trustworthy	“Did you find the virtual person sitting in front of you trustworthy?” *(−3…3)*
Distress	“Did the virtual person sitting in front of you make you feel distressed?” *(−3…3)*
Valence	Please circle the manikin that you think better expresses how you felt while being in the virtual room. Choose one manikin in each of the two figures.
	*Valence manikin*
Arousal	Please circle the manikin that you think better expresses how you felt while being in the virtual room. Choose one manikin in each of the two figures.
	*Arousal manikin*

### 2.5. VR apparatus

The HTC VIVE Pro^4^ virtual reality headset will be used to display the virtual environment. It has a combined resolution of 2,880 × 1,600 pixels (1,440 × 1,600 pixels per eye), a refresh rate of 90 Hz, and a field of view of 110°. The motion tracking equipment which will allow participants to control their virtual body arms in real time is performed using the VIVE trackers (four in total−2 placed on the hands and 2 on the elbows as seen in Figure 1C). The application will run on a computer with a Core [contact] processor and an Nvidia GeForce RTX 3080 graphics card.

### 2.6. Secondary outcomes

We will include additional non-verbal communication tasks outside of VR to assess participants' ability to recognize and perceive non-verbal social cues such facial expressions, biological movements, and voice tone. Motor, cognitive and community functioning domains will be assessed using well-established standardized rating scales and symptom severity and antipsychotic medication usage in all patients will also be accounted for. All clinical, motor, socio-cognitive and community functioning assessments can be found in Table 2.

**Table 2 T2:** Clinical, motor, socio-cognitive and community functioning assessments of participants.

**Secondary outcomes**	**References**
**Psychopathology**	
Brief negative symptom scale	(40)
Positive and negative syndrome scale	(41)
Thought and language disorder scale	(42)
**Motor scales**	
Abnormal involuntary movement scale	(43)
Bush Francis Catatonia rating scale	(44)
Neurological evaluation scale	(45)
Salpêtrière retardation rating scale	(46)
Unified Parkinson's disease rating scale	(47)
**Socio-cognitive assessments**	
Biological motion	(48, 49)
Dot counting task	(50, 51)
EMOREC-B	(52)
Hinting task	(53)
MATRICS consensus cognitive battery	(54)
Postural knowledge test	(55)
Profile of nonverbal sensitivity	(56)
**Community functioning**	
Global assessment of functioning	(57)
Social level of functioning	(58)
Social and occupational functioning assessment score	(59)
University of California, San Diego performance-based skills assessment brief	(60)
**Self-reports**	
Brief assessment of gestures	(61)
Post-VR questionnaire on presence and embodiment	(62)
Self-report of negative symptoms	(63)

## 3. Statistical analysis

Measurements collected from the tracking devices during gesture performance will be analyzed using linear mixed models. These will include upper body rotational data per gesture across all experimental blocks. Data are saved at a frequency of 60 Hz (16 ms). The rotational data between participants and the virtual agent performing the gestures will be compared across time based on distance metrics such as Dynamic Time Warping (DTW) that measures similarity between time series by considering the temporal relationship between rotational vectors. Group (patients and healthy controls) and gesture category (meaningless, intransitive, and transitive), as well as, their interaction will be added as fixed effects, while a single intercept parameter estimated for each participant will be added as random effects. Covariates in the model will also be considered if demographic characteristics such as age, gender or education are different between patients and controls. In addition, differences in symptom severity and motor deficits between inpatient and outpatient participants will also be considered. The Kruskal–Wallis test will be used to assess such differences. In addition, we will apply partial correlation analyses using the spearman method to examine the relationship between gesture performance accuracy in VR with symptom severity, motor, socio-cognitive and community functioning scores, while controlling for medication. This will help in determining if gesture performance accuracy using VR in patients is linked to a specific domain or is generalized across multiple domains.

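### The mixed model has no term for block position or repetition, so any practice or fatigue trend becomes unmodelled error in the category and group-by-category tests; the main group comparison is not affected

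*Protocol article*

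**What the plan says.** Section 2.4 (VR procedures) sets up a blocked, repeated task: "Each block contains 6 different gestures and will be repeated twice during the experiment". On order it says: "All gesture blocks (meaningless, intransitive, and transitive) will be randomized across participants". Practice comes before the test blocks: "After this introductory phase, participants will be trained on the task". The article does not say whether order is free over all presentations, whether the two presentations of a category follow one another, or whether each cycle contains every category once.

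Section 3 (Statistical analysis) pools the repeated data: "These will include upper body rotational data per gesture across all experimental blocks". The fixed effects are listed: "Group (patients and healthy controls) and gesture category (meaningless, intransitive, and transitive), as well as, their interaction will be added as fixed effects". The random part is one term: "a single intercept parameter estimated for each participant will be added as random effects". The only other covariates named are demographic ones, if the groups differ on them, and consideration of inpatient-outpatient differences in symptoms and motor deficits. Position in the sequence and repetition do not appear.

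**The concern.** Block position is a factor that the design creates and the system can record, much like period in a crossover trial. All six gestures of a block share one position, so a trend over the session acts on whole blocks and does not average out within them. A model with only a participant intercept treats that block-level deviation as independent trial noise. If there is a trend, the contrasts between categories, and between groups across categories, become more variable than the model's standard errors show. Precision is lost and the interaction test rejects too often.

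The stake is the reading of the group-by-category result, that is, whether the patients' deficit differs between meaningless, intransitive and transitive gestures. Section 3 gives that interaction a place in the model, although the Introduction states no hypothesis about it.

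**Working it through.** The article gives no variances, drift or power figure, so there is no stated number to reproduce. The check asks how far the stated model's interaction test departs from 5% under a range of assumptions.

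**Inputs from the article.** Section 2.1: "We plan to recruit 60 schizophrenia patients and 60 age and gender matched controls over a 2-year period". Section 2.4: six gestures per block and three categories. Section 3: the model terms quoted above.

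**Assumptions.** Two presentations of each block, so 3 × 2 × 6 = 36 trials per person and 120 × 36 = 4,320 in all. Trial SD is 1. A linear drift of d trial SDs from first to last block is shared by everyone. Three possible ordering schemes are considered.

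**1. Group main effect.** Code position x = 0, 0.2, 0.4, 0.6, 0.8, 1. Every participant has mean position 0.5 whatever the order, so a shared drift adds 0.5d to everyone and cancels between groups.

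**2. Trial noise in one interaction contrast.** The difference of two category means of 12 trials has variance 2/12 = 0.1667 per person. Compared between groups, this is 2 × 0.1667/60 = 0.005556, SD 0.0745.

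**3. Variance V of the difference in mean position between two categories.**
- The within-person variance of x is 2.2/6 − 0.25 = 0.1167. With divisor 5 it is 0.14.
- Free order: two disjoint pairs drawn from six, V = 0.14 × (1/2 + 1/2) = 0.14.
- Consecutive repeats: mean positions are 0.1, 0.5 and 0.9, with variance (0.16 + 0 + 0.16)/2 = 0.16, so V = 2 × 0.16 = 0.32.
- Each cycle contains all categories: the variance within a cycle is 0.04, a difference has 2 × 0.04 = 0.08, and averaging over two cycles gives V = 0.04.

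**4. Inflation.** The true variance of the contrast rises by λ = 1 + d²V/0.1667 = 1 + 6d²V. The model's residual variance rises only to 1 + 36 × 0.1167d²/35 = 1 + 0.12d². With k the ratio of the two, a nominal 5% test on 2 degrees of freedom rejects about 0.05^(1/k) of true nulls, because the chi-square tail on 2 degrees of freedom is exponential.

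| Drift d | Order | λ | SD ratio √λ | k | Rejection |
|---|---|---|---|---|---|
| 0.25 | free | 1.053 | 1.03 | 1.045 | 5.7% |
| 0.25 | consecutive | 1.120 | 1.06 | 1.112 | 6.8% |
| 0.25 | cycles | 1.015 | 1.01 | 1.007 | 5.1% |
| 0.5 | free | 1.210 | 1.10 | 1.175 | 7.8% |
| 0.5 | consecutive | 1.480 | 1.22 | 1.437 | 12.4% |
| 0.5 | cycles | 1.060 | 1.03 | 1.029 | 5.4% |

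**5. Cross-check by simulation of the stated model.** At d = 0.5, separate simulations gave 7.2 to 7.9% under free order (one gave 9.3%), 11.0 to 13.3% with consecutive repeats, and 4.8 to 5.9% with cycles. At d = 0.25 the simulated rates lie at about 5 to 8% over the three schemes. The mean of the interaction contrast was about 0 throughout (largest absolute value 0.0034), so there is no bias.

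**6. With position and group-by-position in the model.** At d = 0.5 the simulated rejection was about 4 to 6% under every ordering. At zero drift the contrast SD barely changed (0.0727 without the terms, 0.0734 with them).

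**7. Drift that differs between participants.** The fixed terms remove only the average drift in each group. If individual drifts vary with SD τ, τ² takes the place of d² in step 4. With τ = 0.5 the last three rows of the table therefore return even after adjustment: 7.8%, 12.4% and 5.4%. Simulations with mean drift 0.5 and SD 0.5 gave about 6 to 8% under free order and up to about 13% with consecutive repeats.

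**The case against.** The strongest reply is that randomised order is the standard protection against order effects and that it works here: the estimates are unbiased. The Introduction hypothesises a group difference in accuracy, which step 1 shows is untouched. Section 2.1 also describes modest aims: "This is an exploratory cross-sectional observational study using VR technology to assess the performance accuracy of different hand gestures". Training before the test blocks should remove some early learning. The article gives no drift, and at 0.25 SD, or with cycle-balanced order, the harm is close to nil. All of this stands, and it limits the weight of the point.

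A second reply is that a condensed article leaves nuisance terms to a fuller plan. This stands only in part. Section 3 does list the fixed and random terms, and the point is about that list.

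A third reply is that the lone participant intercept is the closer cause of the too-small standard error. Step 7 supports this where drift varies between people. The fixed term is still the direct way to remove a shared, recorded trend.

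Three stronger readings are tempting, and the article does not support them:
- That the patient-control comparison is confounded by order. It is not, because everyone completes the same set of blocks.
- That the Discussion's remarks on motor learning predict drift here. They concern rehabilitation evidence from neurological patients and give no size for a change within one session.
- That power for the interaction falls sharply. The precision loss is real (contrast SD 10 to 22% larger at 0.5 SD under free or consecutive order), but raw power for an assumed 0.15 SD interaction under free order stayed at about 0.52 to 0.55 with or without the term. The unadjusted figure is helped by its raised false-positive rate.

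**Conclusion.** The point holds as a minor one. The stated model leaves out a factor that the design itself creates, and any trend over blocks then enters the error of the category and group-by-category tests. The consequence is lost precision and some excess false positives in the interaction test. There is no bias and no effect on the main group comparison.

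At a shared drift of 0.5 trial SD the nominal 5% test runs at about 7 to 8% (free order), 11 to 13% (consecutive repeats) or 5 to 6% (cycles). At 0.25 SD it runs at about 5 to 8%. These figures rest on 60 versus 60, two presentations per block, a linear drift and an assumed ordering scheme; the article supplies only the sample size and the block content. A reader might infer that the study's main conclusion is at risk. The calculation does not show that.

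**What to change.** In Section 3, add block position (1 to 6, categorical), or repetition and position within cycle if the blocks run in two cycles, to the fixed effects of the linear mixed model, together with its interaction with group. Keep group, category and their interaction as planned. State in Section 2.4 which ordering scheme is used, since the size of the problem depends on it.

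Because drift may differ between participants, also consider a participant-by-block or participant-by-category random effect. The fixed term alone then corrects the standard error only in part.

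A group difference at first presentation could be reported, but that is a separate question outside the stated aims and not part of this correction.

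The cost is a sentence or two of wording. Categorical position and its interaction with group use 5 + 5 = 10 degrees of freedom, against about 4,320 − 120 − 4 = 4,196 within-participant residual degrees of freedom. No new data are needed, since block order is known from the randomisation.

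### A participant intercept alone gives unreliable error bars for gesture category and group-by-category, because each category holds different gestures performed repeatedly by everyone

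*Protocol article*

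**What the plan says.** Three parts of the protocol article fix the analysis.

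- **Data and fixed effects (Section 3, Statistical analysis).** The outcome is a distance, such as Dynamic Time Warping, between the participant's and the agent's rotation series. On the data entered: "These will include upper body rotational data per gesture across all experimental blocks". On the fixed part: "Group (patients and healthy controls) and gesture category (meaningless, intransitive, and transitive), as well as, their interaction will be added as fixed effects".
- **Random part (same section).** It is stated in full: "while a single intercept parameter estimated for each participant will be added as random effects". There is no term for the individual gesture, for a participant's profile across categories, or for repeated performances of one gesture. Nothing says that scores are averaged first.
- **Design (Section 2.4, VR procedures; Section 2.1, Study design).** "Each block contains 6 different gestures and will be repeated twice during the experiment". There are three block types, one per category. The target is 60 patients and 60 controls, and the study describes itself as exploratory.

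**The concern.** Every gesture belongs to one category, so category varies between gestures. The stated model puts stable differences between gestures into the residual and treats them as independent noise, although all 120 participants perform the same gestures. It also holds each participant's deviation from their group-by-category mean constant over the three categories, and it treats two performances of one gesture as no more alike than performances of two different gestures.

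These simplifications are hard to believe here. A distance between rotation series should differ between movements of different form. The Introduction links patients' errors to postural knowledge, tool use and social perception, while the transitive category is by definition tool-based. Patients who differ in those impairments should also differ in their category profile.

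At stake are two of the three fixed effects named for the primary outcome. An apparent deficit confined to one type of gesture could be an artefact of the error term, or a real one could be missed.

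**Working it through.** The plan gives no alpha, power, effect size or variance components, so there is no stated figure to reproduce. The check asks how the F tests of the stated model behave when the omitted components exist.

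**Inputs from the protocol article**
- 3 categories × 6 gestures = 18 gestures; × 2 runs = 36 performances per participant (derived; a run count of 2 is one reading of Section 2.4).
- 120 participants × 36 = 4,320 rows.
- Residual df under the stated model: 4,320 − 120 − 4 = 4,196.

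**Assumptions:** balanced data, no true category or interaction effect, two-sided 5%, residual variance 1 unless stated. The components below are chosen for illustration.

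**Formula.** Both tests have 2 numerator df and a critical value of about 2.996. Let R be the expected test mean square divided by the expected pooled residual. The false-positive rate is then about exp(−2.996/R), which is 5% at R = 1.

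**1. Group-by-category, participant-by-category variance v.** The test mean square is 1 + 12v (6 gestures × 2 runs). The component has (120 − 2) × 2 = 236 df, so the pooled residual is 1 + 12v × 236/4,196.

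| v | R | exp(−2.996/R) | Simulated |
|---|---|---|---|
| 0.05 | 1.60/1.034 = 1.55 | 14% | 13% |
| 0.10 | 2.20/1.067 = 2.06 | 23% | 21% |
| 0.20 | 3.40/1.135 = 3.00 | 37% | 37% |

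**2. Category, gestures as a sample of their category, gesture variance g.** The test mean square is 1 + 240g (120 participants × 2 runs). Gestures within category have 15 df, so the pooled residual is 1 + 240g × 15/4,196.

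| g | R | exp(−2.996/R) | Simulated |
|---|---|---|---|
| 0.1 | 25/1.086 = 23.0 | 88% | 86% |
| 0.5 | 121/1.429 = 84.7 | 97% | 96% |

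**3. Group-by-category, gesture variance only.** Both groups perform the same gestures, so gesture main effects cancel from the numerator but still inflate the residual. At g = 0.5, R = 1/1.429 = 0.70, giving 1.4% (simulated 1%). In a second simulation with g = 0.2 and residual 0.5, the rate was 2.3%.

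**4. Category, with the 18 gestures as the whole set of interest.** With gesture variance 0.2 and residual 0.5, the pooled residual is 0.5 + 0.2 × 4,320/4,196 = 0.706. R = 0.5/0.706 = 0.71, giving about 1.5% (simulated 1.4% for category, 1.6% for the interaction).

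**5. Cross-check on another scale.** The second simulation (2,000 data sets per scenario, total variance 1, participant share 0.30) gave:

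| Added component (share of total) | Category | Group-by-category |
|---|---|---|
| None | 6.1% | 4.4% |
| Participant-by-category 5% | 18% | 19% |
| Participant-by-category 10% | 34% | 32% |
| Participant-by-gesture 10% | 7% | 8% |
| Participant-by-gesture 20% | 11% | 11% |
| Group-by-gesture 2% | 4% | 34% |

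With a 10% participant-by-category share, the model's standard error for an interaction contrast was 0.061 against a true SD of 0.099.

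**6. Sensitivity to the row count.** If repetitions are averaged first, there are 2,160 rows and 2,160 − 124 = 2,036 residual df. At v = 0.05, R = (0.5 + 0.3)/(0.5 + 0.3 × 236/2,036) = 0.8/0.535 = 1.50, giving 13.5%. If a block is run three times, there are 6,480 rows and 6,356 residual df. Then R = 1.9/(1 + 0.9 × 236/6,356) = 1.84, giving about 20%. Neither reading removes the problem.

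**7. Overall group effect.** It compares participant means. Participant-by-category and participant-by-gesture variance average into those means and are picked up by the estimated between-participant variance, while gesture main effects cancel. Only a group difference that varies by gesture would escape.

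**The case against.** - **The main question is elsewhere.** The hypothesis in the Introduction is that patients are less accurate overall and that this relates to clinical measures. It names no category or interaction hypothesis, and the study is exploratory. This stands. A reader might infer that the patient-control comparison is invalid; step 7 shows that it is largely protected.
- **The items are fixed.** The task derives from a standardised test, so inference may be meant for these gestures only. This stands as far as it goes: the 86% to 96% rate depends on treating gestures as a sample, and under the fixed-set reading the error reverses. The article does not say which target it intends, and the stated model is right for neither unless gesture variance is negligible.
- **The direction is unknown.** A reader might infer that the interaction test is always too liberal. The documents do not support that: the rate runs from about 1% to 37% with the assumed components.
- **The model is valid on its own terms.** True: with only participant and residual variance, the rates are near nominal. The fault is a likely misspecification, not an arithmetic error.
- **Repetitions may be averaged before analysis.** The text allows this, and it would deal with the participant-by-gesture component. It would not deal with the participant-by-category or gesture components (step 6).
- **This could be left to an analysis plan.** This does not stand, because Section 3 states the random part explicitly.

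**Conclusion.** The concern holds for the category and group-by-category results, as a change that should be made rather than one on which the study depends. Their standard errors are right only if gesture, participant-by-category and participant-by-gesture variances are all near zero, which is implausible for distances computed on movements of different form.

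The two tests fail for different reasons. Group-by-category becomes too liberal through participant-by-category variance and, less strongly, participant-by-gesture variance; gesture variance alone pushes it the other way. The error in the category test depends mainly on whether the gestures represent their category or are the whole target.

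The mechanism follows from the design and does not depend on the assumed figures. The sizes do depend on them, and on balanced data, so they should be read as a range.

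**What to change.** In Section 3, replace the single participant intercept with:

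1. a participant random intercept plus a participant-by-category random term;
2. a gesture effect: a crossed random intercept if inference is to the category, or fixed gesture effects nested in category if inference is to these 18 items, with the choice of target stated. In the fixed version, each category contrast should be defined as a difference between averages over the 6 gestures;
3. a participant-by-gesture random intercept if repetitions enter as separate rows; otherwise state that repetitions are averaged first.

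Use Satterthwaite or Kenward-Roger degrees of freedom. A group slope by gesture can be a sensitivity analysis; a near-maximal random structure is not needed to cure the defect.

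The cost is one paragraph of wording and modest computing. No new data are needed, since recordings are kept per gesture. With a random gesture term, category intervals will be wider, because there are only 6 gestures per category. Singular fits are possible, so the order in which terms are simplified should be fixed in advance.
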